### Nurse practitioners

The nurse practitioners are all qualified nurses with several years of experience and affinity for nephrology. They received extensive education in cardiovascular risk reduction with emphasis on current guidelines, they were familiarized with the contents of the flowcharts and all were uniformly trained in interview techniques to support them in implementing lifestyle-modification and maximizing compliance. Completion of the official Dutch Nurse Practitioner training program was no prerequisite to function as a nurse practitioner in this study.

### Statistical and data analysis

#### Power analysis

To detect a 50% between-group difference in the trial primary endpoint with a pre-estimated 5-year event incidence of 13.5% for the control group [16,41], a power of 80% and a two-sided type I error α of 5%, at least 640 patients will have to be included. Taking into account a possible loss to follow-up of 15%, at least 740 patients will be randomized.

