### Recruitment and screening

All subjects will be recruited from the outpatient nephrology or internal medicine clinic of nine Dutch hospitals. Patients are identified by checking their medical records for compatibility with the inclusion criteria prior to a regular outpatient visit. Renal function will be estimated using the Cockcroft-Gault formula (with a correction for body surface area as of April 15^th ^2005)(appendix A). The Cockcroft-Gault equation has been extensively validated and is generally appreciated as a useful tool to estimate creatinine clearance[28,29]. The physician will give every eligible patient a brief verbal explanation and extensive written information about the study. A week later follow-up by the nurse practitioner will be performed. Upon verbal consent to participate in the study, the patient will be invited to the office. In this visit the in- and exclusion criteria will be checked thoroughly, written informed consent will be acquired and subsequently baseline measurements will be performed. The medical ethics committees of the participating hospitals have approved the conduct of the study.

Recruitment began in April 2004 and is estimated to continue until December 2005. About 60% of patients deemed eligible by their physician and asked to participate in the study, actually participate and are included. The main reasons for non-participation appear to be: reluctance of the patient to changes in drug therapy and inability of the patient to attend the required visits. On December15, 2005 793 patients had been included.

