### Baseline evaluation and randomization

Table 1 summarizes the data collected at baseline evaluation. After the baseline evaluation, the patient will be randomized to either nurse practitioner care or physician care. Randomization to treatment is stratified by center and renal transplant status using a web-based randomization module and performed in predefined blocks of certain numbers of patients.

**Table 1 T1:** Data collection

Visit	Baseline 1	Visit 2	Visit 3	Visit 4	Visit 5
Month	0	3	6	9	12

Informed Consent	x				
Demographic data	x				
Medical history	x				
In- and exclusion criteria	x				
Randomization	x				
Endpoints		x	x	x	x
Weight	x	x	x	x	x
Waist-hip ratio	x				x
Ankle-Brachial Index	x				x
RR and HR in sitting position	x	x	x	x	x
RR 30 minutes Dynamap	x		x		x
Smoking habit	x	x	x	x	x
Medication use	x	x	x	x	x
Three monthly Laboratory evaluation^a^	x	x	x	x	x
Annual Laboratory evaluation ^b^	x				x
ECG	x				x
PWV (Proportion of patients)	x				x
Carotid-IMT (Proportion of patients)	x				x
Questionnaires ^c^	x				x

a: Three monthly Laboratory evaluation: Hematology: Hb, Ht, trombocyte count; Chemistry: sodium, potassium, calcium, phosphate, bicarbonate, urea, creatinine, albumin; Urinalysis: spot urine creatinine, albumin, total protein

b: Annual Laboratory evaluation: Hba1c, uric acid, PTH, total-cholesterol, HDL-cholesterol, LDL-cholesterol, triglycerides; Urinalysis: 24 hr urine sodium, creatinine, albumin, total protein

c: Questionnaires: Quality of Life: SF-36, EQ-5D; Physical activity: SQUASH; Dietary composition; Erectile dysfunction

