#### Group sequential analysis

Group sequential analysis will be used to evaluate the primary endpoints and to monitor the safety data. Sequential analysis is a statistical approach where one conducts significance tests over time as the data are collected. Sequential analysis and its application in clinical trials has been described extensively by Whitehead [42]. The general approach is as follows. A null hypothesis H_0 _and an alternative hypothesis H_1 _are formulated for a suitable measure θ of treatment difference. For this study with a survival type outcome variable, θ is equal to the logarithm of the hazard ratio (HR). H_0 _is formulated as "no difference in the occurrence of the primary endpoints between the two trial arms" or θ = 0 (i.e. HR = 1). The alternative hypothesis H_1 _is formulated as |θ | ≥ log(0.48) = 0.73 group. Two test statistics, Z and V, can be derived depending on the type of response variable. Z is a measure of the treatment difference; for survival data Z is the observed number of events in the control group minus the expected number of events given treatment equivalence (i.e. the number of events that would have occurred if the same proportion of events was found in the intervention group and in the control group).V reflects the amount of information about θ contained in Z; for survival data V is approximately equal to a quarter of the number of events observed. The sequential analysis requires critical boundaries to be specified in advance. These boundaries depend onθ, the type I error α and the power 1-β. For each new group of patients, values of Z and V are calculated and presented graphically by plotting Z against V (see Figure1 for an illustration of a double-sided sequential test). Based on the path of cumulative (Z, V)-points, one of the following three decisions is made:

1) the upper or the lower (continuous) boundary is crossed: stop the data collection and reject the null hypothesis;

2) one of the inner wedge-shaped (dashed) boundaries is crossed: stop the data collection and accept the null hypothesis;

3) continue the data collection: the cumulative data are inadequate to draw a conclusion yet.

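### The printed sample-size figures do not fit together: 640 patients after 15% loss needs 753 randomised, while the stated minimum of 740 leaves 629 (a minor correction)

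*Protocol article*

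**What the plan says.** The Power analysis section gives both the inputs and the results. The aim is "To detect a 50% between-group difference in the trial primary endpoint", with a "pre-estimated 5-year event incidence of 13.5% for the control group", "a power of 80% and a two-sided type I error α of 5"%. From these it concludes that "at least 640 patients will have to be included". It then adds the allowance for loss: "Taking into account a possible loss to follow-up of 15%, at least 740 patients will be randomized". Both 640 and 740 are therefore worded as minimums, and no inflation formula is shown.

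Two other places bear on the point. The abstract plans approximately 800 patients, and the Recruitment and screening section reports that by 15 December 2005 "793 patients had been included".

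**The concern.** If a fraction d of randomised patients is lost and n must remain, the number to randomise is n/(1 − d). With n = 640 and d = 0.15 this is larger than 740. The stated floor for randomisation therefore does not deliver the stated floor for patients remaining at the stated rate of loss.

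This section is the trial's sample-size justification, and 740 is the only randomisation number given as a minimum. A reader, or the data safety monitoring board, would use it to judge whether observed loss is within plan. As printed, it overstates the loss the design tolerates.

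**Working it through.** **Inputs.** From Power analysis: control incidence 13.5% at 5 years; a 50% difference, taken as a relative reduction, so 6.75% in the intervention group; two-sided α 5%; power 80%; minimum 640; loss 15%; minimum randomised 740. Group sequential analysis gives a hazard ratio under the alternative through "≥ log(0.48) = 0.73", which agrees with the ratio implied by the two incidences: ln(1 − 0.0675)/ln(1 − 0.135) = 0.482. That agreement supports the relative reading. Assumption: 1:1 allocation. The article says only that "the patient will be randomized to either nurse practitioner care or physician care" and states no ratio.

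**Step 1: reproduce 640.** The mean incidence is (0.135 + 0.0675)/2 = 0.10125.

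- Pooled two-proportion formula, per arm: [1.960 × √(2 × 0.10125 × 0.89875) + 0.842 × √(0.135 × 0.865 + 0.0675 × 0.9325)]² / 0.0675² = 312.3, so 313 per arm and 626 in total.
- Freedman log-rank formula: events = (1.960 + 0.842)² × [(1 + 0.482)/(1 − 0.482)]² = 64.2, so 65; 65/0.10125 = 642 patients. With a hazard ratio of 0.48 it gives 64 events and 632 patients.

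The printed 640 is thus a reasonable figure for the stated inputs. It is not in dispute.

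**Step 2: the allowance for loss.**

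| Calculation | Result |
|---|---|
| Needed to keep 640 after 15% loss: 640/0.85 | 752.9, so 753 |
| Left from 740 after 15% loss: 740 × 0.85 | 629 |
| Loss that 740 can absorb: 1 − 640/740 | 13.5% |
| Shortfall in patients randomised: 753 − 740 | 13 (1.8% of 740) |
| Shortfall in patients remaining: 640 − 629 | 11 |

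The 13.5% loss equals the control incidence only by coincidence.

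**Step 3: possible origins of 740.**

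- 640 × 1.15 = 736, rounded up.
- 626/0.85 = 736.5, so 737, rounded up.

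Both are compatible with the printed number.

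**Step 4: effect on power** (fixed design, lost patients counted as contributing nothing).

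| Patients remaining | Two proportions | Freedman, hazard ratio 0.482 |
|---|---|---|
| 640 | 80.9% | 80.4% (64.8 events) |
| 629 | 80.3% | 79.7% (63.7 events) |

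The difference is about 0.7 percentage points with either formula.

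**Step 5: enrolment.** 793 × 0.85 = 674 and 800 × 0.85 = 680, both above 640. With 793 included, the tolerated loss is 1 − 640/793 = 19.3%.

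**The case against.** The strongest reply is that nothing practical depends on this. The gap is 13 patients in 740. On the two-proportion formula, power at 629 is still above 80%. The planned analysis is a log-rank test, in which patients lost to follow-up contribute time and events until they are censored, so removing all 15% overstates the harm. Planned and actual enrolment both exceed 753. All of this stands, and it makes the point minor. It does not reconcile 640, 15% and 740: the section words 640 as a minimum, and 740 falls on the wrong side of it. On the Freedman formula, which gives the closest match to 640, power at 629 is just under 80%.

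A reader might infer two stronger things. The first is that the planners used the wrong inflation formula and multiplied 640 by 1.15. The article shows no formula, that product is 736 rather than 740, and a correct division of an unrounded 626 by 0.85 leads to 740 equally well. The second is that the trial is underpowered. The power figures and the enrolment reported in the article do not support that.

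**Conclusion.** The inconsistency is real and follows from three printed numbers alone. At 15% loss, 740 randomised leaves 629, not 640; keeping 640 needs 753; and 740 covers 13.5%. How 740 arose cannot be settled from the article.

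The consequence is minor: about 0.7 points of power at most, leaving it at 79.7% to 80.3% at 629, with no effect on recruitment. The power figures assume 1:1 allocation, a relative reduction of 50%, a fixed design without the planned interim analyses, and no contribution from lost patients. The arithmetic on 640, 15% and 740 needs none of these assumptions.

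**What to change.** Change the final sentence of Power analysis in one of three ways:

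- restate the minimum randomised as 753 (754 for equal arms, if allocation is 1:1);
- keep 740 and state that it covers a 13.5% loss from 640;
- print the unrounded sample size from which 740 was derived, with the formula for the loss allowance.

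Add that the 793 patients included exceed the corrected minimum. The cost is one sentence, with no extra patients and no change to the analysis.

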#### Group sequential analysis

Group sequential analysis will be used to evaluate the primary endpoints and to monitor the safety data. Sequential analysis is a statistical approach where one conducts significance tests over time as the data are collected. Sequential analysis and its application in clinical trials has been described extensively by Whitehead [42]. The general approach is as follows. A null hypothesis H_0 _and an alternative hypothesis H_1 _are formulated for a suitable measure θ of treatment difference. For this study with a survival type outcome variable, θ is equal to the logarithm of the hazard ratio (HR). H_0 _is formulated as "no difference in the occurrence of the primary endpoints between the two trial arms" or θ = 0 (i.e. HR = 1). The alternative hypothesis H_1 _is formulated as |θ | ≥ log(0.48) = 0.73 group. Two test statistics, Z and V, can be derived depending on the type of response variable. Z is a measure of the treatment difference; for survival data Z is the observed number of events in the control group minus the expected number of events given treatment equivalence (i.e. the number of events that would have occurred if the same proportion of events was found in the intervention group and in the control group).V reflects the amount of information about θ contained in Z; for survival data V is approximately equal to a quarter of the number of events observed. The sequential analysis requires critical boundaries to be specified in advance. These boundaries depend onθ, the type I error α and the power 1-β. For each new group of patients, values of Z and V are calculated and presented graphically by plotting Z against V (see Figure1 for an illustration of a double-sided sequential test). Based on the path of cumulative (Z, V)-points, one of the following three decisions is made:

1) the upper or the lower (continuous) boundary is crossed: stop the data collection and reject the null hypothesis;

2) one of the inner wedge-shaped (dashed) boundaries is crossed: stop the data collection and accept the null hypothesis;

3) continue the data collection: the cumulative data are inadequate to draw a conclusion yet.

With a sequential approach a trial can be stopped earlier, on average, than with a fixed sample size approach. Using a sequential design between 460 and 716 patients would have to be included. (The number of patients to be included can not be fixed beforehand because patient data are analyzed cumulatively and a decision is made to stop or to continue the trial according to the interim results.) Due to the large difference between the duration of the inclusion period and that of the follow-up, it will not be possible to implement this potential benefit in the design of the trial. Although the length of follow-up in this trial in relation to the period scheduled for inclusion does not allow for a reduction in sample size other benefits of group sequential analysis remain present. Earlier clarity on the primary endpoint could allow for earlier stopping of the trial and thus result in saving time and funds for other experiments. Also safety related issues, which are to be monitored one-sided, will possibly be identified earlier and in this way patient safety is guaranteed throughout the trial.

### Statistical methods

Group sequential (or interim) analyses will be performed using the double triangular test as described by Whitehead [42] and implemented in the computer program PEST version 4 [43]. The analyses will be performed by an independent data safety monitoring board (DSMB) consisting of a nephrologist, an internist and a statistician. They meet every 6 months to monitor various aspects of the study, including recruitment, adverse events and interim analyses of the primary endpoints.

The results of the study will be analyzed following the 'intention to treat' principle. This means that subjects will be analyzed according to the group they have been allocated to by the randomization. Results will be presented as Kaplan-Meier curves for the two treatments and the difference between the treatments will be analyzed using a log-rank test. For the primary outcome variables the log-rank test will be adjusted for the effect of the cumulative data analyses. Results will be presented for all cause mortality and CV events separately.

The primary analysis of CIMT progression wiw ll be performed using a linear random coefficient (Laird-Ware) model using real visit days, treatment and clinical center as independent variables. For each participant, the intercept and slope of CIMT change over time is assumed to be a normally distributed random variable with different means for the two treatment groups. The mean slope for the nurse practitioner group will be compared to that for nephrologist-care group using linear contrasts and a 5% significance level. Additional exploratory analyses will evaluate the impact of including baseline IMT, lumen diameter, ultrasound reader, and center as additional co-variates.

The data analytic approach to arrive at the PWV outcome variable is similar to that of the CIMT outcome. Adjustments that will be taken into account in the estimates are changes in MAP and changes in heart rate, since both are closely related to PWV.

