**Design:**

MASTERPLAN is a multicenter randomized controlled clinical trial designed to evaluate whether a multifactorial approach with the aid of nurse-practicioners reduces cardiovascular risk in patients with CKD. Approximately 800 patients with a creatinine clearance (estimated by Cockcroft-Gault) between 20 to 70 ml/min, will be included. To all patients the same set of guidelines will be applied and specific cardioprotective medication will be prescribed. In the intervention group the nurse practitioner will provide lifestyle advice and actively address treatment goals. Follow-up will be five years. Primary endpoint is the composite of myocardial infarction, stroke and cardiovascular mortality. Secondary endpoints are cardiovascular morbidity, overall mortality, decline of renal function, change in markers of vascular damage and change in quality of life. Enrollment has started in April 2004 and the study is on track with 700 patients included on October 15th, 2005. This article describes the design of the MASTERPLAN study.

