### Endpoint collection and evaluation

The primary endpoint has been defined as follows, based on experience in other studies run at the UMCU [38,39].

• Myocardial infarction is defined as evident new ischemic changes on an ECG or an established rise and fall pattern of cardiac enzymes.

• Stroke is defined as characteristic clinical symptoms of stroke accompanied by signs of recent ischemia using an appropriate imaging technique (CT-scan or MRI).

• Cardiovascular mortality is defined as death due to myocardial infarction, stroke, ruptured abdominal aneurysm, and terminal heart failure. Also sudden death will be regarded as part of cardiovascular mortality.

All suspected events, which might contribute to the primary endpoint, will be evaluated by an independent endpoint-committee. The committee will evaluate these events using definitions for the different events which are also used in other Dutch trials [38,39].

Secondary endpoints are collected via clinical data, questionnaires or specified procedures. The SphygmoCor system (pulse wave velocity system and blood pressure analysis system, PWV Inc., Sydney Australia) is used to assess PWV and to analyze the arterial pulse contours. Pulse contours will be obtained by applanation tonometry at the carotid, radial and femoral arteries. Independent investigators blinded for treatment allocation of the subject will perform evaluation of recorded data. CIMT assessment will be performed using B-mode ultrasonography of both carotid arteries with a 7,5-MHz linear array transducer to assess the presence of plaques in the common carotid artery, bifurcation and internal carotid artery. All measurements will be recorded on video and evaluated off-line by independent evaluators blinded for treatment allocation of the patient [40].

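### Kaplan-Meier curves for a composite that counts only cardiovascular deaths overstate each arm's 5-year incidence; the bias is modest and the primary test is unaffected

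*Protocol article*

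**What the plan says.** The Design paragraph of the abstract states: "Primary endpoint is the composite of myocardial infarction, stroke and cardiovascular mortality". Endpoint collection and evaluation limits the fatal component to "death due to myocardial infarction, stroke, ruptured abdominal aneurysm, and terminal heart failure", and its next sentence adds sudden death. No other death counts towards the primary endpoint.

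Statistical methods fixes the display, "Results will be presented as Kaplan-Meier curves for the two treatments", and the comparison: "the difference between the treatments will be analyzed using a log-rank test". For the primary outcome the log-rank test is adjusted for the interim looks. The same paragraph adds: "Results will be presented for all cause mortality and CV events separately". Group sequential analysis takes the log hazard ratio as the measure of effect.

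A 5-year incidence appears in one place only, as a planning input under Power analysis: "pre-estimated 5-year event incidence of 13.5% for the control group". The article does not say how non-cardiovascular death is handled in the curves and names no cumulative-incidence method.

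**The concern.** A patient who dies of a non-cardiovascular cause can no longer have the primary event. Kaplan-Meier treats that patient like one lost to follow-up, who could still have it. One minus the curve therefore estimates the risk in a setting where nobody dies of other causes. As a statement of how many patients had an event by five years it is too high in each arm whenever such deaths occur.

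Such deaths are to be expected: follow-up is five years, there is no upper age limit, and overall mortality is itself a secondary outcome. Readers will naturally compare the end of the curves with the 13.5% in the power analysis and may subtract one arm from the other. What is at stake is the accuracy of absolute risks taken from the main figure, not the test of the primary hypothesis.

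**Working it through.** **Inputs from the article.** Control 5-year incidence 13.5% and a 50% reduction, read as 6.75% in the intervention arm (Power analysis); follow-up T = 5 years (Design); hazard ratio 0.48 under the alternative (Group sequential analysis); 640 patients, 740 after 15% loss (Power analysis).

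**Assumed, because the article gives no figure.** Net 5-year non-cardiovascular mortality q between 3% and 20%, where net means the mortality if that cause acted alone; constant cause-specific hazards.

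**The plan's own figures.** ln(1 − 0.0675)/ln(1 − 0.135) = 0.482, which agrees with 0.48. Comparing 13.5% with 6.75% at 80% power and two-sided 5% gives 313 per arm, 626 in total (pooled proportions, no continuity correction). Freedman's formula with hazard ratio 0.482 gives 65 events, and 65/0.10125 = 642. Both are close to 640, so the stated size reproduces. None of this depends on how the curves are drawn.

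**Formulas.** With event hazard λ and competing hazard μ:
- One minus Kaplan-Meier at 5 years: 1 − exp(−5λ)
- Actual cumulative incidence: λ/(λ+μ) × [1 − exp(−5(λ+μ))]
- λ(control) = −ln(0.865)/5 = 0.02901; λ(intervention) = −ln(0.9325)/5 = 0.01398; μ = −ln(1 − q)/5

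**Worked case, q = 10% in both arms.** μ = 0.02107.
- Control: 0.02901/0.05008 × (1 − 0.865 × 0.90) = 0.5792 × 0.2215 = 12.83%
- Intervention: 0.01398/0.03505 × (1 − 0.9325 × 0.90) = 0.3988 × 0.16075 = 6.41%
- Actual difference 6.42 points, against 6.75 from Kaplan-Meier

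**Equal non-cardiovascular mortality (Kaplan-Meier shows 13.5% and 6.75%, difference 6.75).**

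| q | Actual incidence, control / intervention | Excess of Kaplan-Meier, control / intervention (points) | Actual difference (points) |
|---|---|---|---|
| 3% | 13.30% / 6.65% | 0.20 / 0.10 | 6.65 |
| 5% | 13.17% / 6.58% | 0.33 / 0.17 | 6.59 |
| 10% | 12.83% / 6.41% | 0.67 / 0.34 | 6.42 |
| 15% | 12.48% / 6.24% | 1.02 / 0.51 | 6.25 |
| 20% | 12.13% / 6.06% | 1.37 / 0.69 | 6.07 |

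The difference is overstated by 0.10 to 0.68 points, or 1.5% to 11% in relative terms.

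**Unequal non-cardiovascular mortality (Kaplan-Meier difference still 6.75).**

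| q, control / intervention | Actual difference (points) | Bias of Kaplan-Meier difference (points) |
|---|---|---|
| 20% / 5% | 5.55 | +1.20 |
| 10% / 5% | 6.25 | +0.50 |
| 5% / 10% | 6.76 | −0.01 |
| 5% / 20% | 7.11 | −0.36 |

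The sign is therefore not fixed.

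**Taking 13.5% as the actual incidence instead.** Kaplan-Meier would show 13.8%, 14.2%, 14.6% and 15.0% at q = 5%, 10%, 15% and 20%. If the same percentages are the proportions who actually die first of another cause, it shows 13.9%, 14.3%, 14.7% and 15.2%. The implied hazard ratio stays between 0.480 and 0.482 over q = 3% to 20%.

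**Scale.** With 370 per arm, the 95% half-width for the difference is 1.96 × √[(0.135 × 0.865 + 0.0675 × 0.9325)/370] = 4.3 points.

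**The case against.** The strongest reply is that nothing inferential changes. Censoring non-cardiovascular deaths is correct for a log-rank comparison of cause-specific hazards, and that comparison is the planned test. The hazard ratio, the Z and V statistics, the boundaries and the sample size are likewise unaffected. All of this stands.

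A reader might infer that the trial will report an inflated absolute risk reduction and number needed to treat. The article does not support that: it plans neither, and 13.5% is only a planning input whose method of estimation cannot be checked here. Nor is a difference read from the curves always too large, as the unequal-mortality cases show. A reader might also take the separately presented CV events to be non-fatal events, so that every death competes. The text does not say so; they may simply be the composite set beside all-cause mortality.

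It can also be said that the size is small against a half-width of 4.3 points, that it rests on assumed mortality, and that all-cause mortality shown alongside partly reveals the competing event. These points are fair and lower the weight of the finding. They do not remove it: the bias within each arm is systematic and does not shrink with more patients, and an all-cause curve beside the composite does not correct it.

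Finally, a fuller analysis plan may add cumulative-incidence estimates. But the article does not leave the display open. It names Kaplan-Meier, so the point concerns a stated choice and not missing detail.

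**Conclusion.** The point holds as a minor one about presentation and estimation. For the composite as defined, Kaplan-Meier curves overstate the actual 5-year incidence in each arm. In the control arm the excess is about 0.2 to 0.7 points for 3 to 10% non-cardiovascular mortality and about 1.4 points at 20%; in the intervention arm it is about half of that. A difference taken from the curves would be biased by an amount and in a direction that depend on how non-cardiovascular deaths fall between the arms.

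The sizes rest on assumed non-cardiovascular mortality and constant hazards. The upward direction within each arm rests on neither. It requires only that some non-cardiovascular deaths occur and are censored, which is inferred from the choice of estimator because the article does not state it.

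**What to change.** In Statistical methods, replace the Kaplan-Meier display of the primary composite with Aalen-Johansen cumulative incidence curves by arm, with non-cardiovascular death as the competing event. Do the same for any CV-event display that does not count all deaths, with the deaths not counted as events as the competing event. Take any reported 5-year risks, and any difference between them, from these curves. Report the number of non-cardiovascular deaths by arm. Keep Kaplan-Meier for all-cause mortality and keep the sequentially adjusted log-rank test as the primary test.

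The cost is about one sentence of analysis wording and a few lines of code. No new kind of data should be needed: overall mortality is already an outcome, and suspected primary events, including possible cardiovascular deaths, already go to the endpoint committee. The displayed incidences become slightly lower.

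### Randomisation is stratified by centre and transplant status, but the primary log-rank test and the sequential Z and V are described without strata, and the CIMT/PWV model omits transplant status (small power cost, test still valid)

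*Protocol article*

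**What the plan says.** On allocation (Protocol article, Baseline evaluation and randomization): "Randomization to treatment is stratified by center and renal transplant status using a web-based randomization module". Patients come from the "outpatient nephrology or internal medicine clinic of nine Dutch hospitals" (Recruitment and screening), so there are up to 9 × 2 = 18 strata.

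On the primary endpoint (Statistical methods): "the difference between the treatments will be analyzed using a log-rank test". The one stated modification is that "the log-rank test will be adjusted for the effect of the cumulative data analyses". Neither sentence mentions strata.

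On monitoring (Group sequential analysis): Z is described as control-arm events observed minus those expected if both arms had the same event proportion, and V as roughly one quarter of all events. Both are written as pooled quantities, in a passage introduced as a general account of the method.

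On vascular markers (Statistical methods): CIMT progression is to be analysed with a "linear random coefficient (Laird-Ware) model using real visit days, treatment and clinical center as independent variables". Exploratory analyses then look at "including baseline IMT, lumen diameter, ultrasound reader, and center as additional co-variates". Transplant status is in neither list. For PWV, "The data analytic approach to arrive at the PWV outcome variable is similar to that of the CIMT outcome", with changes in mean arterial pressure and heart rate added.

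**The concern.** Stratified allocation forces the arms to be balanced on centre and transplant status. If these factors predict the outcome, that balance lowers the true variability of the treatment comparison. A test that ignores the strata does not use the reduction. Its variance is too large, it rejects a true null hypothesis less often than 5%, and it gives up some power.

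The article is also uneven: one randomisation factor enters the CIMT model, the other does not, and neither is named for the primary test. No reason is given.

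At stake is a small amount of power in a trial sized at 80% for a halving of risk, whose authors themselves expect dilution of the group difference (Limitations of the study). The choice also bears on monitoring. A (Z, V) path is compared with boundaries at six-monthly meetings, so whether Z and V are pooled or summed over strata should be fixed beforehand and should match the final test.

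**Working it through.** **1. Reproduce the planned size.** Inputs from Power analysis: control 5-year risk 13.5%, a 50% reduction (to 6.75%), 80% power, two-sided 5%, N = 640. The hazard ratio is ln(1 − 0.0675)/ln(1 − 0.135) = 0.482, matching the 0.48 in Group sequential analysis. Freedman's formula gives (1.960 + 0.842)² × (1.482/0.518)² = 64.2, so 65 events. With a mean risk of (0.135 + 0.0675)/2 = 0.10125, N = 65/0.10125 = 642. The two-proportion formula gives 626. The stated 640 is reproduced, with no allowance for stratification in either direction. Expected events are 640 × 0.10125 = 65, or 65/18 = 3.6 per stratum on average.

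**2. Primary test, simulation at N = 640.** Assumed: nine centres of similar size, permuted blocks of 4 within centre × transplant stratum, 5-year follow-up without loss, no interim looks, 3,000 runs (15% transplant share) or 4,000 runs (30% share). Each cell gives unstratified / stratified by transplant only / stratified by centre × transplant.

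| Transplant share | Transplant HR | SD of centre log-hazard | Power, % | Type I error, % |
|---|---|---|---|---|
| 15% | 1 | 0 | 81.5 / 81.4 / 81.1 | 5.4 / 5.5 / 5.4 |
| 15% | 1.5 | 0.2 | 81.7 / 81.7 / 81.8 | 4.5 / 4.6 / 4.7 |
| 15% | 2 | 0.3 | 82.1 / 82.5 / 81.8 | 4.1 / 4.1 / 4.4 |
| 15% | 3 | 0.5 | 80.5 / 81.3 / 81.9 | 4.1 / 4.6 / 4.8 |
| 30% | 2 | 0.3 | 81.3 / 81.6 / 81.6 | 4.6 / 4.7 / 4.9 |
| 30% | 3 | 0.5 | 80.7 / 81.5 / 82.0 | 4.0 / 4.3 / 4.7 |

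Simulation standard error at 3,000 runs: √(0.05 × 0.95/3000) = 0.4 points for type I error and √(0.81 × 0.19/3000) = 0.7 points for power. Full stratification changes power by −0.4 to +1.4 points.

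**3. Primary test, simulation at N = 740.** Assumed: 15% loss, 15% transplant share, nine centres, 2,500 runs. Unstratified against stratified power is 84.0% and 83.6% with no factor effect, and 82.7% and 82.8% with weak factors. With transplant HR 3 and centre SD 0.7 it is 79.0% and 81.0%, with type I error 4.0% and 5.0%. An SD of 0.7 is a large spread: the central 95% of centre hazards then covers a factor of exp(2 × 1.96 × 0.7) = 15.5. With SD 0.5 the factor is exp(1.96) = 7.1.

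**4. CIMT and PWV slopes.** Suppose power is 80% with transplant status accounted for; the article states no power for these outcomes. Let p be the transplant share and d the difference in mean slope by transplant status, in SDs of the slope within a transplant group. The share of slope variance explained is R² = p(1 − p)d² / [1 + p(1 − p)d²]. If the arms are balanced on transplant status, power without it is Φ(1.960 + 0.842 − 1.960/√(1 − R²)).

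Example with p = 0.15 and d = 0.5: R² = 0.0319/1.0319 = 0.031, and Φ(2.802 − 1.991) = 79.1%.

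For p from 10% to 30%:

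- d = 0.25: 79.6–79.8%
- d = 0.5: 78.5–79.4%
- d = 1: 74.1–77.5%

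So the loss is 0.2 to 1.5 points, rising to 2.5 to 6 points only if transplant status shifts the slope by a full SD. Balance within the subsets of about 150 (CIMT) and 300 (PWV) patients is a further assumption.

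**The case against.** The strongest reply is that the article never says the log-rank test is unstratified. It says nothing about strata, its account of Z and V is a general description, and a condensed design article may leave this detail to an analysis plan that is not shown. That stands as far as it goes: if such a plan stratifies the log-rank test, this part of the point falls. It does not cover the CIMT model, whose covariates are listed explicitly with one randomisation factor in and the other out.

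A second reply is that an unstratified log-rank test is a legitimate choice. It matches the Kaplan-Meier curves to be shown and the marginal risks behind the sample size, and it avoids spreading about 65 events over up to 18 strata. This also stands. It is why the remedy needs a pooling rule, and why a smaller hazard ratio effect from an unstratified analysis is a difference between marginal and conditional measures, not an error.

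A reader might infer more: that the planned test is invalid, or that the stated power is lost. The figures do not support either. Type I error is not inflated, and unstratified power is 80.5–82% at N = 640 in every scenario tried, falling to 79.0% only under the most extreme assumptions at N = 740 with loss. A reader might also infer that the factors were chosen because they are prognostic. The article gives no reason for the choice.

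**Conclusion.** The point holds as a low-cost improvement. The factors that govern allocation are not carried through to the analysis as described: no strata for the primary test or for Z and V, and no transplant status in the CIMT model. For PWV the same follows only by reference, since its approach is called similar and its covariates are not listed in full.

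The size is small. With strongly prognostic factors the primary test is slightly conservative (about 4%) and loses about 1 to 2 points of power; with weak factors it loses nothing. The slope analyses lose at most about 1.5 points unless transplant status has a very large effect on progression. These sizes rest on assumed transplant shares (15–30% for the primary test, 10–30% for slopes), assumed factor effects, an assumed block size where one was needed, and a fixed-sample test in place of the sequential one in the N = 640 simulation.

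**What to change.** - **Primary test.** State that the final log-rank test is stratified by centre and transplant status, with small centres pooled by a rule fixed before any comparison by arm. If strata are still too sparse, stratify by transplant status alone; in the strong scenarios at N = 640 this recovers 0.8 of the 1.3 to 1.4 points.
- **Monitoring.** Compute Z and V as sums over the same strata, so that the stopping decision and the final inference use one statistic.
- **CIMT and PWV.** Add transplant status and its interaction with time. The comparison is of mean slopes, and a main effect alone would mainly shift intercepts. In the same paragraph, remove centre from the list of additional exploratory covariates, since it is already in the primary model.

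The cost is analysis wording; both factors are recorded at randomisation. If the factors are not prognostic, stratifying costs about 0.4 points of power (81.5% to 81.1%, and 84.0% to 83.6%), within simulation error. The hazard ratio becomes conditional on strata and not marginal, which should be said when it is reported beside the unstratified Kaplan-Meier curves.
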